## Abstract

**Background:**

The Cochrane review on the effectiveness of speech and language therapy for aphasia following stroke suggests intensity of therapy is a key predictor for outcome. Current aphasia services cannot provide intervention at the intensity observed within trial contexts because of resource limitations. Telerehabilitation could widen access to speech-language pathologists (SLPs) in geographically remote contexts and reduce the time spent on travel by the therapist and patient. The current academic literature within this field is in its infancy, with few trials of speech and language therapy (SLT) delivered by videoconference. Our pilot randomized controlled trial (RCT) will explore feasibility aspects and effectiveness of telerehabilitation for aphasia in addition to standard SLT.

**Method/design:**

Our study is a pragmatic, exploratory, pilot randomized controlled trial, where participants will be randomized to a telerehabilitation group or a control group. Both groups receive standard SLT (usual care) but the telerehabilitation group receives an additional 5 h of telerehabilitation per week over 4 weeks through videoconference. This additional telerehabilitation focuses on spoken language with an emphasis on word naming. We aim to include 40 patients in each group, with inclusion criteria being aphasia any time post stroke. Participants will be assessed blindly at pre-randomization (baseline), and 4 weeks and 4 months after randomization. The primary endpoint is naming ability 3 months after the completed intervention, measured by the Norwegian Basic Aphasia Assessment (NGA) naming subtest. Secondary endpoints include other subtests of the NGA, the VAST (Verb and Sentence Test) subtest sentence production, Communicative Effectiveness Index (CETI) and the Stroke and Aphasia Quality of Life scale (SAQOL-39). Experiences of patients and SLPs with telerehabilitation are assessed using questionnaires and semi-structured interviews. Statistical between group comparisons will be in line with an intention-to-treat analysis.

**Discussion:**

This pilot RCT of intensive language training by videoconference will contribute new scientific evidence to the field of aphasia telerehabilitation. Here, we describe our trial which will explore the feasibility of telerehabilitation for aphasia as an intervention, our choice of primary and secondary outcome measures and proposed analyses. Our trial will provide information for the development and delivery of future definitive RCTs.

**Trial registration:**

ClinicalTrials.gov, ID: NCT02768922. Registered on 11 May 2016. Last updated on 17 November 2017.

**Electronic supplementary material:**

The online version of this article (10.1186/s13063-018-2588-5) contains supplementary material, which is available to authorized users.

## Background

Today, stroke stands as a major and leading cause of disability worldwide. Each year, one estimates that about 11,000 people in Norway acquire their first stroke [1]. In Norway, stroke is the most common cause of disability in the older population, with a stable incidence for the last decade due to better preventive treatment and acute management [1]. An aging European population in combination with an improvement in the survival rates of stroke is expected to put an increased burden on the health care system in the years to come.

One of the most devastating consequences of stroke is aphasia, a disturbance in language function which can affect the ability to speak and includes difficulties with speech production, auditory comprehension, as well as reading and writing. It affects one third of stroke survivors [2], where about 60% of the patients show consistent communication impairment 1 year post stroke [3]. Aphasia impacts on the rehabilitation process, affecting rehabilitation outcomes in a negative manner. The presence of aphasia following stroke is a negative predictor for return to workforce [4]. People with aphasia report significantly worse health-related quality of life (HRQL) than stroke survivors without aphasia [5]. Hence, aphasia affects stroke survivors’ social life by isolating them from social networks and limiting social participation [6]. Furthermore, aphasia impacts on significant others, describing third-party disability in family members [7]. Effective rehabilitation for aphasia is vital to recovery.

As the future holds an increasingly aged population, the urgency to develop evidence-based, cost-effective interventions to improve rehabilitation of people with aphasia is profound [8]. The aim of aphasia rehabilitation is an improvement in speech and language functions, where speech and language therapy (SLT) is considered to be “gold standard.” Several studies claim that intensive SLT improves outcomes in aphasia [9–11]. The updated Cochrane review from 2016 on the effects of SLT for aphasia following stroke, provides evidence of the effectiveness of SLT in terms of improved functional communication, reading, writing and expressive language compared to no access to therapy [8]. This meta-analysis furthermore concludes that there is some evidence that therapy at high intensity, high dose or over a longer period may be beneficial compared to lower intensity, lower dose or over a shorter period of time [8]. Today, a wide range of different forms of therapy exists, from constraint-induced language therapy (CILT) and functional-orientated therapy to phonological, semantic and cognitive-linguistic approaches. To date, the evidence for the best therapeutic approach, and details about timing, frequency, duration, intensity and dose, is still unclear for the overall aphasia population.

Access to SLT services, the recruitment and retention of speech-language pathologists (SLPs) remains a problem worldwide [12]. In rural countries like Norway, providing tailored aphasia rehabilitation of sufficient intensity and duration is a challenge. An early start to rehabilitation, meeting the Norwegian national guidelines of ≥ 5 h of SLT per week [13], seems not to be provided for reasons as the lack of SLPs and a limited capacity for aphasia services in the municipalities [14]. There is a unique opportunity to use telemedicine solutions for providing therapy. Telerehabilitation represents a future service delivery model for aphasia beyond the traditional gold standard of “face-to-face” treatment [15]. Telerehabilitation has been defined as rehabilitation services delivered via information and communication technology, and is categorized as rehabilitation services provided at a distance [16, 17]. It has the potential to widen the access to SLPs with promise of better and more equitable services. However, the academic literature on aphasia telerehabilitation is yet in its infancy, with substantial gaps in the scientific evidence of the feasibility and effectiveness of this therapy approach. This seems to be the case for stroke rehabilitation in general, as a Cochrane review of all types of telerehabilitation services for stroke has concluded that there is limited trials and evidence to guide practice [18]. Studies of the use of videoconference in aphasia interventions is especially lacking, with only one pilot RCT on the effectiveness of telerehabilitation by videoconference included in the published Cochrane review on aphasia following stroke [19]. Thus, the need to provide high-quality RCTs to contribute scientific evidence and knowledge to this relatively new field of aphasia research is a priority.

There are barriers and advantages with telerehabilitation activities in SLT as elaborated in a recent review [20]. A great advantage is higher availability of treatment facilitating shorter waiting lists and reducing potential delay of treatment. Telerehabilitation can reduce traveling time and costs for both patient and therapist. As treatment takes place in the patient’s home environment, the rehabilitation can be goal orientated toward the patient’s everyday life, with greater involvement of family and caregivers [20]. Telemedicine uses computer-based technology, which might enable the use of interactive computer-based therapy programs, videogames or social media [21]. Following stroke, significant fatigue and motor dysfunction can make traveling to receive therapy a challenging task. By receiving therapy in the home, patients with fatigue can focus their energies on aphasia rehabilitation rather than the journey to the rehabilitation centre [15]. Favorable patient satisfaction with telerehabilitation has been described [22, 23]. Despite these advantages, there are several barriers that hinder the routine implementation of telerehabilitation into a clinical setting. To date, we lack cost-benefit and cost-effectiveness analyses on telerehabilitation. There are ethical issues and threats to privacy and confidentiality to address. The lack of infrastructure, technical and/or personal support, funding of equipment and the lack of reimbursement are other issues to consider [20].

We previously conducted a feasibility study to explore the feasibility of delivering SLT by videoconference [24]. Tailored speech-language therapy was tested through videoconference in four patients with aphasia. Patient satisfaction and feasibility aspects were mapped through logs, questionnaires and semi-structured interviews. Aphasia rehabilitation via videoconference was found to be acceptable to both patient and therapist, and considered sustainable and feasible with regards to technical, logistic, patient and data safety aspects [24]. In this article we present the protocol of a pragmatic, exploratory, pilot randomized controlled trial (RCT) of standard SLT augmented by additional hours of SLT by videoconference compared to standard SLT alone. This pilot trial targets a larger, randomized sample size recruited across a number of sites, providing a better understanding of feasibility and new technical arrangements beyond our earlier feasibility study.

Due to ethical issues we have chosen a design were we compare the effects of aphasia telerehabilitation alongside standard SLT (usual care) with standard SLT only. To date, we have limited evidence of the effectiveness of telerehabilitation, which limits the application of SLT via videoconference as a treatment option.

### Objectives and aims

The objective of this pragmatic exploratory pilot RCT is to investigate the feasibility and effectiveness of speech and language training by videoconference given in addition to standard aphasia rehabilitation (usual care).

The primary and main aim of this study is to pilot the RCT of the clinical effectiveness of augmented speech-language therapy intervention for people with aphasia after stroke delivered by videoconference over 4 weeks (in addition to standard aphasia rehabilitation). We will explore whether augmented speech-language therapy by videoconference can improve word naming 4 months post randomization, when compared to standard rehabilitation (usual care).

Secondary aims of our pilot trial are to inform our intervention content, delivery, technology as well as software and training requirements. We will also gather data to enhance our understanding of anticipated recruitment, intervention adherence and dropout and future sample size calculations and our choice of outcomes. We also aim to explore the links between our intervention and naming, functional communication, quality of life and other language impairments than naming at 4 months post randomization, and whether it is sustainable and feasible with regards to ethical, technical, logistic, patient and data safety aspects.

## Methods/design

### Design

The study will use a pragmatic prospective RCT design (phase II exploratory trial), where outcomes will be compared for people with aphasia post stroke, randomly allocated to a telerehabilitation group or a control group. The telerehabilitation group will receive 5-h speech-language therapy via videoconference per week over 4 weeks, in addition to standard aphasia rehabilitation (usual care). The control group will receive standard speech-language therapy (usual care) only. The amount of standard aphasia rehabilitation will be logged for all participants. The patients will be assessed at inclusion and before randomization (baseline), and at 4 weeks and 4 months post randomization. Testing will be blinded. The protocol conforms to the Consolidated Standards of Reporting Trials (CONSORT) guidelines for pragmatic trials [25] and the guideline extensions for randomized pilot and feasibility trials [26]. The trial design is depicted by the flow diagram in Fig. 1. The timeline for study enrollment, intervention and assessment is illustrated in Fig. 2 (Standard Protocol Items: Recommendations for Interventional Trials (SPIRIT) Figure). A SPIRIT Checklist and CONSORT Checklist is included as Additional files 1 and 2.

**Fig. 1 Fig1:**
[figure not shown]
Flow diagram trial design

**Fig. 2 Fig2:**
[figure not shown]
Trial schedule of enrollment, intervention and assessment (Standard Protocol Items: Recommendations for Interventional Trials (SPIRIT) Figure)

### Ethics approval

The trial has been approved by the Norwegian Regional Committee South East for Medical and Health Research Ethics (reference number: 2015/2129, approval received in December 2015).

### Participants

We aim to recruit 80 participants with the diagnosis of aphasia following stroke. The patients will be recruited from the stroke units at Oslo University Hospital, Akershus University Hospital, Østfold Hospital and Bærum Hospital. Patients who are admitted for rehabilitation at Sunnaas Rehabilitation Hospital will also be included. In addition, patients or those on the waiting list at Sunnaas Rehabilitation Hospital will be invited to participate. We will also seek to recruit patients from other rehabilitation institutions, and in cooperation with speech-language pathologists in the region of Oslo, Østfold and Akershus. The recruitment of patients is limited to these areas due to geographical and practical aspects. Expressions of interest in participation will also be invited from members of the Aphasia Association of Norway (user organization).

### Inclusion criteria

Participants will be included if they meet the following criteria:Patients with aphasia following stroke (any time post stroke)Aphasia including naming impairment (percentile score of 70 or lower on the Norwegian Basic Aphasia Assessment (NGA) naming subtest)Norwegian as their main language

### Exclusion criteria

Participants will be excluded from the study if they meet any of the following criteria:Age below 16 yearsPatients who are unable to perform 5 h of speech-language therapy per week due to medical (including extensive hearing and/or vision impairment) or cognitive reasonsPatients who score > 70 percentile score on the NGA naming subtestPatients with traumatic brain injury (TBI)

Patients with previous stroke are considered to meet inclusion. Patients will be included regardless of whether they are left or right handed. Regarding time post stroke, no limits were set in order to ensure a valuable sample size for this RCT, given the timeframe and geographical set up for the recruitment. This will result in a less homogenous sample, but increase ecological validity.

## Procedures

### Identification

Staff at recruitment sites will screen patients for eligibility, inform potential participants about the project and refer them to Sunnaas Rehabilitation Hospital for further investigation. Potential participants, who are patients at Sunnaas Rehabilitation Hospital, will receive information about the project and an invitation to take part in the trial. Members of the Aphasia Association of Norway will receive information about the study in a flyer and a brochure inviting them to contact the research team if they are interested in participating.

### Screening for eligibility, baseline assessment and recruitment

Detailed information about the project will be provided and the research investigator will seek informed consent before carrying out baseline testing. The Informed Consent Form and Information Sheet are accessible for people with aphasia. Relatives and caretakers will be carefully informed about participation. Eligibility will be established by an ambulatory visit ([name], [name]) to the stroke unit, patient’s home or rehabilitation institution. Their eligibility will be confirmed by using clinical observations, medical information and language tests. The baseline assessment consists of the NGA subtests and the Verb and Sentence Test (VAST) subtest sentence production. If the potential participant is excluded, an explanation that the project is not suitable for the patient will be given. The number of those screened, but not included after screening, will be recorded along with the reason for exclusion. When included in the project, the participant’s demographic data will be collected including age, gender, relationship status and housing conditions. Relevant medical data, time post onset of stroke and type and location of stroke will be charted. The Modified Rankin Scale will describe the functional status of the patients, and be registered at each assessment time point (baseline, 4 weeks and 4 months; Fig. 1). Participants will be contacted up to three times for participation in outcome and follow-up assessment. No further data will be collected for those who discontinue study participation.

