### Key secondary endpoint(s)

Key secondary endpoints are other language functions 4 months post randomization measured by the NGA subtest “comprehension” and “repetition.” In addition, the VAST subtest sentence production [28], assesses the ability of verb and sentence production beyond words. Functional communication is assessed using the Communicative Effectiveness Index (CETI) [29]. These endpoints are scored/collected immediately after the intervention (4 weeks) and at the 4-month post randomization follow-up to detect any extended effect of the intervention.

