### Other secondary endpoints

Quality of life will be assessed by using the Stroke and Aphasia Quality of Life scale (SAQOL-39) [30]. The SAQOL-39 is a quality of life scale developed specifically with regard to persons with aphasia. In addition, the experiences of patients, relatives and therapists with the telerehabilitation services and their participation within the trial will be gathered using questionnaires and semi-structured interviews with both SLPs and selected participants. Adverse events, including technical challenges, will be logged.

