## Statistical analysis

Data will be analyzed on an intention-to-treat basis. Descriptive statistics will be applied and the characteristics of the sample will be described. The trial is a longitudinal study with continuous repeated measurements. The data will be analyzed by using mixed models. A mixed model is preferred to the more traditional repeated measures analysis of variance (ANOVA) because of its advantages in the way in which it accommodates missing values. Data will be examined for differences over time and between groups. Subgroup analysis will be performed to explore factors considered to affect the outcome of the trial like differences in time since onset of stroke or demographic and stroke-related factors. Qualitative data collected from semi-structured interviews will be suitably coded for qualitative responses to be categorized and examined.

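### The written baseline battery omits CETI and SAQOL-39, and the text gives neither scale a time point before randomisation

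*Protocol article*

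**What the plan says.** All references are to the protocol article.

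- **Baseline content** (*Screening for eligibility, baseline assessment and recruitment*): "The baseline assessment consists of the NGA subtests and the Verb and Sentence Test (VAST) subtest sentence production". The same section adds demographic and medical data and the Modified Rankin Scale, which will "be registered at each assessment time point (baseline, 4 weeks and 4 months; Fig. 1".
- **CETI** (*Key secondary endpoint(s)*): "Functional communication is assessed using the Communicative Effectiveness Index (CETI". The timing for this group of endpoints is: "These endpoints are scored/collected immediately after the intervention (4 weeks) and at the 4-month post randomization follow-up to detect any extended effect of the intervention".
- **SAQOL-39** (*Other secondary endpoints*): "Quality of life will be assessed by using the Stroke and Aphasia Quality of Life scale (SAQOL-39". No time point is attached.
- **General schedule** (*Design*): "The patients will be assessed at inclusion and before randomization (baseline), and at 4 weeks and 4 months post randomization". No instrument is singled out.
- **Analysis** (*Statistical analysis*): mixed models for repeated continuous measurements, with the aim that "Data will be examined for differences over time and between groups".
- **Schedule by visit**: the caption of Fig. 2 reads "Trial schedule of enrollment, intervention and assessment (Standard Protocol Items: Recommendations for Interventional Trials (SPIRIT) Figure". The figure itself is not reproduced in the text available for this review.

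**The concern.** The sentence on the baseline battery is worded as a closed definition, and two of the trial's own endpoints are outside it. A site that follows the text would measure CETI and SAQOL-39 only after randomisation. Three things would then be lost for functional communication and quality of life.

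1. **Change across the intervention.** The first measurement would come at 4 weeks, when the intervention ends. Differences over time could then mean only the change from 4 weeks to 4 months.
2. **Adjustment for the starting level.** The randomisation list is unrestricted, and patients may enter at any time after stroke, so the sample will be mixed. A chance difference in starting level on these scales could not be measured directly, and the variation between patients that a baseline value would explain would stay in the error term.
3. **Planning information.** A stated purpose of the pilot is to inform later sample size calculations and the choice of outcomes. Without a baseline, it cannot estimate the baseline-outcome correlation or the variability of change for these two scales.

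Timing relative to allocation also matters. Allocation is phoned once baseline data are recorded, and participants are not blinded. A scale outside the defined battery has no written safeguard against being completed after the allocation is known.

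**Working it through.** **Step 1. Is a baseline stated anywhere for each instrument?**

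| Instrument | Baseline stated by name in the text | Follow-up times stated |
|---|---|---|
| NGA naming, comprehension, repetition | Yes (screening and baseline section) | 4 months for naming; 4 weeks and 4 months for comprehension and repetition |
| VAST sentence production | Yes (same section) | 4 weeks and 4 months |
| Modified Rankin Scale | Yes (same section, separate sentence) | 4 weeks and 4 months |
| CETI | No | 4 weeks and 4 months |
| SAQOL-39 | No | None by name |

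The timing sentence under *Key secondary endpoint(s)* also leaves out baseline for the NGA subtests and VAST, which do have one. Its silence therefore proves nothing about CETI. What separates CETI and SAQOL-39 from the rest is that no other sentence supplies their baseline.

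**Step 2. The plan's own figure.** The article gives no calculation for CETI or SAQOL-39. Its only one is for a within-group paired comparison on NGA naming: 8 percentile points, SD 18.17, 5% significance, 80% power, 32 participants. Taking 18.17 as the SD of change, (18.17 × (1.645 + 0.842) / 8)² = 31.9, so 32 is reproduced with a one-sided 5% test. This point does not depend on that figure. Only the group sizes are carried forward: 40 per group planned, and 32 if dropout is 20% (32 / 40 = 0.80).

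**Step 3. What a missing baseline would cost.** Let r be the correlation between a scale's baseline and its follow-up value. The documents do not give r, so 0.3 to 0.7 is an assumption. The comparator is an analysis with no baseline covariate at all.

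- Variance of the group difference after adjustment, relative to no adjustment: 1 − r²
- Width of the confidence interval, relative: √(1 − r²)
- Equivalent sample-size factor for having no baseline: 1 / (1 − r²)
- Detectable difference in SD units (two-sided 5%, 80% power): (1.960 + 0.842) × √(2 / n) × √(1 − r²)

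| | No baseline | r = 0.3 | r = 0.5 | r = 0.7 |
|---|---|---|---|---|
| 1 − r² | 1 | 0.91 | 0.75 | 0.51 |
| CI width, relative | 1 | 0.95 | 0.87 | 0.71 |
| Sample-size factor | – | 1.10 | 1.33 | 1.96 |
| Detectable difference, n = 40 per group | 0.63 | 0.60 | 0.54 | 0.45 |
| Detectable difference, n = 32 per group | 0.70 | 0.67 | 0.61 | 0.50 |

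The loss therefore runs from about 10% to 96% more patients for the same precision.

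**Step 4. How many participants can still benefit.** *Trial status* reports 50 randomised out of a target of 80, so 80 − 50 = 30 remained at the time of writing.

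**The case against.** A reader might infer that CETI and SAQOL-39 definitely have no value before randomisation. The documents do not establish that.

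- Fig. 2, which would settle the matter, is not available here, and an article may leave the schedule by instrument to such a figure.
- The battery sentence sits among the eligibility tests and may be meant to name only the language tests. The Modified Rankin Scale, added in the same section, shows that the sentence does not list all baseline data.
- The general schedule and the repeated-measures analysis fit with baseline collection of every scale.

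These points stand, and they rule out the categorical reading. They do not remove the issue. The article does name the baseline items, separately where needed, and nothing in the text supplies these two.

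A reader might also infer that follow-up comparisons without a baseline are biased, or that imbalance could not be checked at all. Neither follows. A randomised comparison of follow-up values is unbiased, and its confidence interval already allows for chance imbalance. The baseline NGA subtests, VAST, the Modified Rankin Scale and time since stroke can be compared between groups or used as covariates. To the extent that they predict CETI and SAQOL-39, they would recover part of the lost precision, so the figures above are upper values for each assumed r. With r = 0.3 the loss is small in any case.

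**Conclusion.** The point holds as a gap in the written plan. The text lists only the NGA subtests and VAST as the baseline assessment and gives no time point before randomisation for CETI or SAQOL-39, which sits badly with the three-visit schedule and the analysis over time. Whether the data are in fact missing cannot be decided from the text.

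If the plan is carried out as written, the consequence is reduced precision, no view of change across the intervention period, and no adjustment for the scale's own starting level. The size is equivalent to about 10% to 96% more patients, given an assumed correlation of 0.3 to 0.7 and no other baseline covariate. Validity of the randomised comparison is not at stake. The affected endpoints are secondary ones in a pilot, and the primary endpoint has a stated baseline. The matter is still worth correcting because the remedy is cheap and applies at a visit that already takes place.

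**What to change.** First establish whether CETI and SAQOL-39 are already collected before randomisation.

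- **If they are not:** add both to the baseline battery in *Screening for eligibility, baseline assessment and recruitment*, to be completed before allocation is phoned, for all participants not yet randomised. Enter the values as the baseline time point in the mixed model. With baseline modelled as one of the repeated measurements, participants enrolled earlier stay in the analysis without a baseline value. Report how many have one.
- **If they are:** correct the battery sentence, and state that both scales are completed before allocation is known.

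In both cases, align *Design*, *Key secondary endpoint(s)*, *Other secondary endpoints* and Fig. 2, and give SAQOL-39 its time points by name.

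The cost is two instruments the trial already uses at an existing visit, so a slightly longer baseline session. If they are added now, the full benefit reaches only about 30 of the 80 participants, and the gain in precision will be correspondingly smaller than the table shows.
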